## Abstract

**Background:**

The high rate of cannabis use among patients with first-episode psychosis (FEP), as well as the associated negative impact on illness course and treatment outcomes, underlines the need for effective interventions in these populations. However, to date, there have been few clinical treatment trials (of pharmacological or psychological interventions) that have specifically focused on addressing comorbid cannabis use among these patients. The aim of this paper is to describe the design of a study protocol for a randomized controlled trial in which the objective is to assess the efficacy of a specific cognitive behavioral therapy program for cannabis cessation in patients with FEP compared to standard treatment (psychoeducation).

**Methods/design:**

This is a single-blind randomized study with 1 year of follow-up. Patients are to be randomly assigned to one of two treatments: (1) specific cognitive behavioral therapy for cannabis cessation composed of 1-hour sessions once a week for 16 weeks, in addition to pharmacological treatment scheduled by the psychiatrist, or (2) a control group (psychoeducation + pharmacological treatment) following the same format as the experimental group. Participants in both groups will be evaluated at baseline (pre-treatment), at 16 weeks (post-treatment), and at 3 and 6 months and 1 year of follow-up. The primary outcome will be that patients in the experimental group will have greater cannabis cessation than patients in the control group at post-treatment. The secondary outcome will be that the experimental group will have better clinical and functional outcomes than the control group.

**Discussion:**

This study provides the description of a clinical trial design based on specific cognitive behavioral therapy for cannabis cessation in FEP patients, aiming to improve clinical and functional outcome, as well as tackling the addictive disorder.

**Trial registration:**

NCT02319746 ClinicalTrials.gov Identifier. ClinicalTrials.gov Protocol and Results Registration System (PRS) Receipt Release Date: 15 December 2014.

**Electronic supplementary material:**

The online version of this article (doi:10.1186/s13063-016-1507-x) contains supplementary material, which is available to authorized users.

## Background

Substance misuse is a common comorbid problem in patients with first-episode psychosis (FEP), cannabis being the most commonly abused substance together with alcohol in this population [1]. The prevalence of cannabis use among patients with FEP is notably high, at around 65.7% [2]. This has led to the hypothesis that its use may have a role in the etiology and evolution of psychosis. It has been found that cannabis use may act as a risk factor influencing age of onset of psychosis [3–8]. Further, young people who abuse cannabis have a higher risk of developing psychosis than non-abusers, with an earlier age of onset of psychosis [9]. The risk of developing psychosis is also related to an early age of onset of use [3, 9–11], and to the severity of use [3, 9], with a frequency- and dose-dependent response, especially in vulnerable individuals [3, 12], increasing the risk in the general population.

Recently, it has also been suggested that cannabis abuse in adolescence can cause alterations in the endocannabinoid system (ECS) and that these alterations may be related to a higher incidence of psychosis and to some of the symptoms presented. Specifically, some research has shown that frequent use of cannabis can cause inhibition of the signaling pathways of the main endocannabinoid, anandamide, in schizophrenia patients but not in healthy individuals [13]. It has also been reported that FEP patients who are cannabis users have cognitive deficits associated with structural abnormalities of brain areas with a high level of expression of cannabinoid receptor type 1 (CB1) [14, 15]. Further, it has been shown that the intake of exogenous cannabinoids could alter synaptic plasticity mediated by the ECS, possibly affecting brain maturation during adolescence, and in turn, neurodevelopmental processes [16].

The ECS is an endogenous homeostatic system with multiple physiological functions and is activated in response to various different stimuli and under different neuropathological conditions. It is composed of a series of lipid mediators, known as endocannabinoids, anandamide and 2-arachidonoylglycerol being the most studied; their two classical receptors coupled to G protein, CB1 and cannabinoid receptor type 2 (CB2); and enzymes responsible for its synthesis, *N*-acyl-phosphatidylethanolamine-selective phospholipase C (NAPE-PLC) and diacylglycerol lipase (DAG-L), and degradation, fatty acid amide hydrolase (FAAH) and monoacylglycerol lipase (MAG-L).

Some studies have linked the ECS with psychotic illness, especially focusing on CB1 and CB2. In particular, lower expression of CB1 has been observed in several brain regions of individuals with schizophrenia [17] and it has also been shown that CB2 loss of function (due to polymorphisms such as *Q63R*) is associated with an increased susceptibility to schizophrenia [18]. Remission of symptoms in schizophrenia has also been associated with significant changes in messenger ribonucleic acid (mRNA) levels of CB2 in peripheral blood mononuclear cells [19]. With respect to other components of the ECS, there is much less information, but alterations in the levels of anandamide have been found in the cerebrospinal fluid of patients with schizophrenia [20].

There is empirical evidence for an influence of cannabis on the course and outcome of psychosis [21, 22]. Cannabis use in early psychosis is correlated with poor adherence to pharmacological treatment [2, 23, 24], the severity of psychotic symptoms [22] and the risk of relapse [2, 21, 23, 24]. Moreover, patients with FEP who use cannabis have a poorer functional outcome at follow-up [22, 25–27]. On the other hand, patients with FEP who stop using cannabis experience a slow but steady improvement over time in clinical and functional outcome [21].

Cannabis use, due to its influence on the development and prognosis of the disease, has become a target for the prevention and treatment of patients with FEP. Such patients, unlike chronic psychotic patients, show a greater variation in the frequency and intensity of cannabis use and greater motivation for change at baseline [28]. Therefore, it is essential to intervene in the early stages of the disease, before cannabis use becomes established. What is more, early intervention may be able not only to reduce but also to detect this type of substance abuse in patients with FEP.

In a systematic review, Ruiz de Azúa García et al. [29] concluded that several studies have shown that psychoeducation as an adjuvant to pharmacological treatment is effective in improving negative symptoms and functionality (Lambeth Early Onset Team Study, UK; Personal Assessment and Crisis Evaluation, Australia; OPUS Scandinavia, Denmark; Early Psychosis Prevention and Intervention Centre, Australia). Evidence suggests that cognitive behavioral therapy may also be effective in FEP [30]. However, despite the recognized clinical consequences of cannabis use in early psychosis [3–6], only a few trials have evaluated clinical treatments as a specific intervention to reduce cannabis use in this population. These studies have investigated interventions based on motivational interviewing [31] or combined interventions based on motivational interviewing and cognitive behavioral therapy [32–35]. Generally, the results obtained failed to clearly indicate whether the interventions were effective in terms of reducing cannabis use and/or improving clinical outcomes at follow-up. The exception was the study conducted by Madigan et al. [34], in which patient quality of life improved at post-treatment. Further, the small sample sizes and the absence of an appropriate treatment-as-usual control condition in these studies indicate that it is not possible to draw definite conclusions.

From reviewing the literature, we conclude that there is an urgent need to develop effective specific interventions to reduce cannabis use as part of comprehensive treatment programs for patients with psychosis. Overall, the effectiveness of interventions and the type of approach used are unclear [31–35]. There is also a need for interventions based on more precise knowledge of individual differences in patterns of use as well as of factors that maintain or inhibit substance abuse in young people with FEP.

The main aim of this article is to describe the design of a randomized controlled trial focused on comparing the efficacy of a specific cognitive behavioral therapy program for cannabis cessation with standard treatment in patients with FEP who are cannabis users. The study design, assessment and intervention program are described.

The specific objectives of the study are:To assess whether a specific cognitive behavioral therapy program for cannabis cessation is associated with a greater reduction in use of cannabis than standard treatmentTo assess whether this type of program for cannabis cessation is associated with better outcomes of the psychotic disorder (i.e., reduction in symptoms and improvement in psychosocial functioning) in the follow-up than standard treatmentTo analyze the relation between cannabis abstinence and clinical and functional outcomes of patientsTo determine whether there are systemic alterations in the components of the ECS and, if so, whether a specific cognitive behavioral therapy program for cannabis cessation is able to normalize such alterationsTo assess whether normalization of elements of the ECS is directly related to reductions in symptoms and improvements in psychosocial functioning attributable to the proposed specific treatment

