### Participants

FEP patients who are cannabis users and meet the inclusion criteria (listed below) are to be included and randomly assigned to one of the two treatment groups. The sample size calculation was performed using data published in the literature related to the main theme of the study (Bonsack et al., 2011 [31]; Edwards et al., 2006 [32]; Hjorthøj et al., 2012; Madigan et al., 2013 [34]) and using Ene 2.0 software. To achieve a power of 80% to detect differences from the null hypothesis, H0: *μ*1 = *μ*2, using a bilateral Student’s *t* test for two independent samples, with a significance level of 5%, we need to include 30 patients in the experimental group and 30 patients in the control group, meaning a total of 60 patients for the study.

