#### Inclusion criteria

The study inclusion criteria for both groups are:Being diagnosed as having had a first psychotic episode: (i.e., schizophrenia, schizophreniform disorder, schizoaffective disorder, delusional disorder, bipolar disorder, atypical psychosis, brief psychotic disorder, or major depressive disorder with psychotic symptoms) according to the revised fourth edition of *Diagnostic and Statistical Manual of Mental Disorders, Fourth Edition, Text Revision* (DSM-IV-TR) [36]Being a regular cannabis user (Table 1):

**Table 1 Tab1:** Classification of cannabis use for selection of participants

Severity of consumption	DSM-IV-TR^a^ criteria for abuse or dependence	Europ-ASI^b^ scores
Dependence	Meet at least minimal DSM-IV-TR criteria for cannabis dependence	8–9
Abuse	Meet ≥1 DSM-IV-TR criteria for cannabis abuse	4–7
Use	Meet DSM-IV-TR criteria for cannabis abuse but not the duration criterion (≥12 months) or ≥12 months of use but do not meet any DSM-IV-TR criteria for cannabis abuse	2–3
No use	No significant symptoms	0–1

^a^Revised Fourth Edition of the Diagnostic and Statistical Manual of Mental Disorders (DSM-IV-TR) [37]

^b^European Addiction Severity Index (Europ-ASI) [37,38]Dependence or abuse of cannabis according to *Diagnostic and Statistical Manual of Mental Disorders, Fourth Edition, Text Revision* (DSM-IV-TR) criteria [36].Dependence or abuse of cannabis according to the scores of the European Addiction Severity Index (EUROP-ASI) [37, 38] (scores of 4 to 7: abuse; scores of 8 to 9: dependence)Aged between 15 and 40 years. In the case of minors (under 18 years of age), written informed consent will be requested from their parents or guardiansBeing in remission from a first psychotic episode (the patients being required to be in remission, without any relapses in a period no more than 5 years from the first psychotic episode)

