
#### Biological variables

To assess whether the treatment program is able to normalize any changes in the components of the ECS, peripheral blood mononuclear cells (10 ml of venous blood anticoagulated with ethylenediaminetetraacetic acid (EDTA)) are to be collected at baseline, at post-treatment and at 3 and 6 months and 1 year of follow-up. In peripheral blood mononuclear cells, the following elements of the endogenous cannabinoid system are to be measured: synthesis enzymes (NAPE-PLD, DAG-L), degrading enzymes (FAAH, MAG-L), and receptors (CB1 and CB2) by Western blot (protein) and reverse transcription-polymerase chain reaction (mRNA).

Toxins in urine are assessed with an immunochromatographic test to detect drug metabolites at baseline, at sessions 4 and 8 of the psychological treatment, post-treatment, and at 3 and 6 months and 1 year of follow-up.

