#### Statistical analysis

IBM SPSS version 23 will be used for the statistical analysis. The sociodemographic characteristics of the patients will be analyzed using descriptive statistics. Differences between the two intervention groups (cognitive behavioral therapy versus psychoeducation) will be analyzed using the χ^2^ test (or Fisher’s test where *n* ≤5) for categorical variables and the Student’s *t* test or Mann-Whitney *U* test (depending on the distribution of the data) for continuous variables.

The differences in cannabis use reduction between two intervention groups will be analyzed using Student’s *t* test and/or the Mann-Whitney *U* test and mixed models. Effect sizes will be calculated for differences in cannabis abstinence based on Cohen’s *d* or *r* [60] for Student’s *t* test and the Mann-Whitney *U* test, respectively. The results will be interpreted as small if *d* values are between .2 and .49, medium if *d* values are between .5 and .79, and large if *d* values are higher than .8.

Differences in efficacy between the interventions in terms of clinical and functional outcomes of patients will be analyzed with repeated measures models (baseline, post-treatment, 3 and 6 months and 1 year of follow-up) and logistic regressions.

Furthermore, whether cannabis abstinence is associated with better clinical and functional outcomes will be analyzed using linear regression models for continuous dependent variables, and Poisson regression models for categorical dependent variables.

Finally, the biological data of patients will be studied in conjunction with clinical data using multivariate analyses. Specifically, the possible alterations in the components of the ECS and the influence of the specific cognitive behavioral therapy program for cannabis cessation on the normalization of ECS will be analyzed using repeated measures models, mixed models or analysis of covariance. Further, the relation between normalization of elements of the ECS and improvement in symptoms and psychosocial functioning, attributable to the specific treatment, will be assessed by regression models.

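### Objectives 4 and 5 ask whether the endocannabinoid system is altered and then normalised, but the design describes no reference against which either could be judged

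*Protocol article*

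**What the plan says.** In the Background, the list of specific objectives includes, as its fourth, to "determine whether there are systemic alterations in the components of the ECS and, if so, whether a specific cognitive behavioral therapy program" can normalise them. The fifth asks whether that normalisation is related to better symptoms and functioning.

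The Biological variables section repeats the aim: "To assess whether the treatment program is able to normalize any changes in the components of the ECS, peripheral blood mononuclear cells" are collected at baseline, post-treatment, 3 months, 6 months and 1 year. Six elements are measured (two synthesis enzymes, two degrading enzymes, and the receptors CB1 and CB2), each as protein and as mRNA.

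The Statistical analysis section takes up possible alterations together with "the influence of the specific cognitive behavioral therapy program for cannabis cessation on the normalization of ECS", and names the methods: "normalization of ECS will be analyzed using repeated measures models, mixed models or analysis of covariance". The relation between normalisation and clinical improvement is then left to regression models.

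On who is enrolled, the Participants section says that "FEP patients who are cannabis users and meet the inclusion criteria (listed below) are to be included and randomly assigned"; no group outside the two arms is mentioned. The Inclusion criteria, which apply to both groups, require "Being a regular cannabis user (Table 1"), specified as cannabis abuse or dependence. Under Intervention programs, the control group is made up of the same kind of patient, receiving psychoeducation and medication.

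**The concern.** *Alteration* and *normalisation* are statements relative to a normal level. The article sets a two-step question (is the system altered and, if so, does the therapy correct it?), yet everyone enrolled belongs to the population whose normality is in question. The control arm is a control for treatment, not a biological reference.

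This is a mismatch between stated objectives and stated design, rather than detail that an article leaves to a fuller document. The objectives, enrolled groups, sample size, assays, time points and model families are all given, and they do not fit together. A statistical analysis plan cannot supply reference data from a sample that contains none.

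At stake is the interpretation of the biological part of the trial. Carried out as written, the analysis would produce a change or an arm difference, and the wording of the objectives would lead it to be reported as normalisation of an alteration that was never shown.

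**Working it through.** **Inputs.** Sample: 30 experimental and 30 control patients (Participants). Population: patients with cannabis abuse or dependence only (Inclusion criteria). Markers: 6 elements × 2 assay types = 12, at 5 time points (Biological variables). Models: repeated measures, mixed models or ANCOVA, then regression (Statistical analysis). The article gives no effect size, SD or reference value for any ECS marker, so there is no stated figure to reproduce for these objectives.

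**Step 1: count the reference observations.** 30 + 30 = 60 enrolled, and all 60 are allocated to treatment arms. 60 − 60 = 0 are left to supply a normal level.

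**Step 2: what the models can identify.** For one marker, let R be the normal level and s the patients' mean departure from it at baseline. Let c be the mean change in the control arm and e the additional change due to the experimental therapy.

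- Baseline mean, both arms: R + s
- Later mean, control: R + s + c
- Later mean, experimental: R + s + c + e
- Within-arm changes: c and c + e
- Arm difference in change: (c + e) − c = e

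The data identify the sum R + s, and c and e. They do not separate R from s. *Altered* means s ≠ 0, which cannot be tested without R.

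**Step 3: whether a change is toward normal.** The therapy brings the marker nearer to normal only if |s + c + e| < |s + c|. As an assumed illustration, take c = 0 and e = −0.5 SD:

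- s = +1: the departure goes from 1 to 0.5, toward normal
- s = 0: from 0 to 0.5, away from normal
- s = −1: from 1 to 1.5, away from normal

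The trial would observe the same e in all three cases.

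**Step 4: check by simulation.** Assumptions: a standardised marker, 30 per arm, all patients shifted by the same amount from an unmeasured norm, a two-sided 5% t test between arms at baseline, and 20,000 runs per shift.

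| Shift from norm (SD) | Rejection rate |
|---|---|
| 0 | 4.8% |
| 0.5 | 5.2% |
| 1 | 4.9% |
| 2 | 5.0% |

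The rate stays at the nominal 5% whatever the shift, so the between-arm comparison carries no information on whether the patients are abnormal.

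**Step 5: whether the background supplies R.** The Background contrasts schizophrenia patients with healthy individuals for anandamide signalling, but anandamide is not among the six measured elements. Lower CB1 expression is cited for brain regions, not blood cells. CB2 mRNA change in peripheral blood mononuclear cells is linked to symptom remission, but no direction or level is given. For the other components the article itself says that much less is known. No normal level for the planned assays follows from any of this.

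**Step 6: objective 5.** Its explanatory variable is normalisation, which Steps 2 and 3 show to be undefined here. The regression becomes well defined if change in the marker replaces it. ECS change and clinical change both arise after randomisation, so that regression estimates an association.

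**The case against.** Several points on the other side are sound.

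- **The biological analysis is not empty.** A reader might infer that objectives 4 and 5 can yield nothing. That goes too far: the randomised effect of the therapy on each component is estimable with the models named, and so is the association between ECS change and clinical change. Only the claims of abnormality and of movement toward normal are out of reach.
- **The word *attributable*.** A reader might infer that the article presents the ECS–outcome association itself as caused by treatment, because the analysis paragraph ends "attributable to the specific treatment, will be assessed by regression models". In both places where the word occurs it most naturally describes the clinical improvement, and the ECS link is called a relation. The text is at most ambiguous and does not support that charge.
- **Direction of change.** It is tempting to say that any rise or fall could be called normalisation. The Background does give an expected direction for CB1, though in brain only, so the statement is too broad.
- **Multiplicity.** Twelve markers invite a remark about chance findings. That problem would be the same with a healthy reference group, so it does not measure this defect, and its handling is commonly left to the analysis plan.
- **A reference may exist elsewhere.** The article is condensed and the assays are run at a separate university. A range could sit in the full protocol or laboratory documents, so the supportable statement is that none is described, not that none exists.

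Patients who become abstinent also offer a contrast within the trial. It is not randomised, is confined to patients and is not a norm. None of these points supplies what objective 4 needs as worded.

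**Conclusion.** The point holds in a limited form. Objective 4 poses a question that the described design cannot answer: 0 of 60 participants provide a reference value, and no range or cut-off is described for the blood-cell assays. Objective 5 fails only in so far as it uses the same undefined term; with marker change in its place it is a feasible analysis of association.

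The conclusion rests on the article as the only source, and on reading *alteration* and *normalisation* in their ordinary sense of departure from, and return to, a normal level. It does not depend on any assumed effect size.

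The consequence is confined to the biological objectives. The Abstract defines the primary outcome as cannabis cessation and the secondary outcome as clinical and functional status; ECS markers belong to neither, and both are unaffected.

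**What to change.** Reword, and fix the estimand to match.

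1. **Objective 4:** to estimate the between-arm difference in change from baseline in each ECS component. For example, later value = b0 + b1 × arm + b2 × baseline value, reporting b1 with its 95% CI, or the equivalent contrast from a mixed model.
2. **Objective 5:** to describe the association between change in ECS components and change in symptoms and functioning. For example, clinical change = a0 + a1 × ECS change + a2 × arm + a3 × baseline ECS + a4 × baseline clinical score. Read a1 as an association, with no claim of mechanism.
3. Replace the terms for alteration and normalisation in the objectives, in Biological variables and in Statistical analysis to match, and label the 12 markers exploratory.

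**Alternative:** if the full protocol or laboratory documents already hold a reference range for the same assay in the same cell type, cite it before the data are analysed and define *altered* and *normalised* from it. A separate reference group would also address the question as posed, but that is a change of design, and its size cannot be calculated because no ECS effect size or SD is given.

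**Cost:** the rewording touches two objectives, one sentence on biological samples and one analysis paragraph. It needs no extra samples, visits or staff. The price is a more modest claim.
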